### Structured medical notes review

We will carry out a structured review of patient medical notes (electronic and paper-based) for the two sample groups described in section Sample size. From these, we will construct a medical summary, looking specifically at patient-centred and system-based variables associated with decisions around ICU admission. We will use a modified version of the Hogan *e*
*t*
*al* qualitative note review techniques.^22^ We will then conduct a thematic analysis of the extracted data.^23^ It is expected that from within the themes the additional variables will be identified. Along with the *as yet unknown* variables, the following data will be extracted:

Primary diagnosis.Comorbidities and medical history (where not available from previous admissions).Any treatment limitations put in place and the reasons for these, including ‘Do not attempt resuscitation’ documents.Current medication.Radiological imaging.Point-of-care blood gas analysis.Clinical Frailty Score.^24^

### Qualitative methods

Qualitative data (eg, information in free text) will be analysed thematically, using methods of constant comparison.^25^ A coding framework will be constructed to assist in understanding of the data. We will use NVivo software (QSR International, www.qsrinternational.com) to support the qualitative analysis process.

### Patient safety and public involvement

As an observational study of patient records with no intervention, adverse events related to research interventions are not possible. In the event that inadequate care is identified during the structured medical note review, local NHS trust protocols will be followed. Reviewers will act in accordance with the General Medical Councils Good Medical Practice Guidelines (2013). This action includes acting immediately if a patient is not receiving basic care to meet their needs. If patients are at risk because of inadequate premises, equipment or other resources, and policies or systems, we will correct the matter if possible and raise our concerns in line with workplace policy. All measures will be documented as per local policies. The HAVEN project has had two lay members on the management committee throughout. They have been involved in regular discussions regarding the aims and remit of the HAVEN project.

## Discussion

### Main findings

This study will use structured medical notes review on ward patients misclassified by HAVEN to identify variables that may enhance performance. Any identified variables will be systematically introduced into our score development pipeline to evaluate whether they improve score performance.

### Strengths and limitations of the study

This study is part of a project-wide process to document the development of the HAVEN system such that it is thorough, transparent, repeatable, reportable and the methodology could be useful for other groups developing similar technology.

Unplanned ICU admission is an outcome measure subject to bias, such as the decision-making of individual physicians, local practice guidelines and bed availability.^26 27^ This study is limited to one hospital and the results may not be generalisable to other hospitals. Variables identified from the thematic analysis may not be available in the EPR and therefore unable to improve the performance of the HAVEN risk score. Likewise, patients with no previous admissions to the John Radcliffe Hospital will have no available comorbidity data, potentially limiting the performance of the risk score in these patients. To assess the impact of these missing data, we will undertake subgroups analyses in those patients with/without prior admissions.

While a significant proportion of ICU admissions are referred directly from the emergency department (ED), the HAVEN system was designed specifically for ward patients needing the attention of the critical care team. By excluding these ED referrals, we are reducing the number of eligible patients for this study.

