### The HAVEN risk score

The HAVEN risk score is calculated using both *static* and *dynamic* variables extracted in real time from the EPR.

Static variables refer to patient-level data available at admission: age, gender, comorbidities (classified according to the Elixhauser comorbidity index^17^) and Hospital Frailty Risk Score.^18^ As diagnostic coding in the UK occurs after a patient has been discharged, the comorbidity index and frailty scores are calculated using a patient’s admissions over the previous 2 years. Score performance in patients with no previous admissions (and potentially undocumented comorbidities) will be evaluated separately.

Dynamic variables refer to measurements taken repeatedly during hospital admission, that is, laboratory results and vital signs. The HAVEN risk score is currently updated according to the most recent measurements of: albumin, bilirubin, C reactive protein, haemoglobin, platelets, white cell count, potassium, sodium, urea, creatinine, heart rate, systolic blood pressure, respiratory rate, body temperature, a neurological status assessment using either the Alert-Verbal-Painful-Unresponsive scale or the Glasgow Coma Scale, peripheral oxygen saturation from pulse oximetry (SpO_2_) and the estimated fraction of inspired oxygen.^19^ A patient’s HAVEN score is re-calculated each time a new dynamic variable is received by the system and the score is further adjusted for the time since hospital admission.

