#### Sample size

We will sample two subgroups of patients:

False High Rank (FHR).False Low Rank (FLR).

The FHR group will consist of patients ranked highly by HAVEN but who were not admitted to the ICU. To identify this group, we will record the five highest-ranked patients on the HAVEN system at 09:00 each morning of the study. After 48 hours, we will remove any patients who were subsequently admitted to the ICU. The remaining patients’ records will be reviewed.

The FLR group will be identified at the end of the study and consist of all patients who had an unplanned ICU admission during the study period and were not present in any of the daily high-ranking groups. These patients’ records will also undergo a medical notes review.

The study will run for 4 non-consecutive weeks with expected recruitment of between 130 and 150 patients.

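### Comparing patients with and without prior admissions describes score performance in each group but cannot isolate the impact of missing comorbidity data

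*Protocol article*

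**What the plan says.** The section on the HAVEN risk score explains where the history inputs come from: "the comorbidity index and frailty scores are calculated using a patient’s admissions over the previous 2 years". It then promises only a stratified description: "Score performance in patients with no previous admissions (and potentially undocumented comorbidities) will be evaluated separately".

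The section on strengths and limitations goes further. It says that "patients with no previous admissions to the John Radcliffe Hospital will have no available comorbidity data, potentially limiting the performance of the risk score", and then gives a purpose and a method together: "To assess the impact of these missing data, we will undertake subgroups analyses in those patients with/without prior admissions".

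Two other sections matter for the remedy. Under the structured medical notes review, comorbidities that earlier admissions do not supply are extracted from the notes, but only for two groups: "We will carry out a structured review of patient medical notes (electronic and paper-based) for the two sample groups". These are the False High Rank (FHR) and False Low Rank (FLR) patients. Under sample size, the first group starts from a daily list ("we will record the five highest-ranked patients on the HAVEN system at 09:00 each morning of the study"), and correctly high-ranked patients then leave it: "After 48 hours, we will remove any patients who were subsequently admitted to the ICU". The article plans no re-scoring of patients with the history inputs altered.

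**The concern.** The impact of missing data is a question about the same patients with and without the missing inputs. The stated method compares different patients. Those with no recent admission are not simply the recently admitted with their coded history deleted. They may have less comorbidity to miss, and their age and acute illness may differ.

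If so, the comparison could blame missing history for a case-mix difference, or hide a real loss behind one. The article presents missing coded history as a possible limit on the score, and it hopes that other groups will reuse the methodology. A mistaken reading of this comparison could therefore be passed on.

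**Working it through.** **The plan's own figure.** Five patients a day for 4 weeks gives 5 × 7 × 4 = 140 daily list places, inside the expected recruitment of 130 to 150. Repeat appearances, removed ICU admissions and the number of FLR patients are not given, so the range cannot be derived. This point does not depend on it.

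**Why the comparison cannot separate the two effects.** Write A for a performance measure, such as the area under the ROC curve (AUC). By the two sections above, the prior-admission group is always scored with coded history and the other group always without it. (This reads prior admission as one within the 2-year look-back.) Then

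gap = A(prior, history used) − A(no prior, history blank)
= [A(prior, history used) − A(no prior, history known)] + [A(no prior, history known) − A(no prior, history blank)]
= case-mix term + missing-data term.

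The plan observes only the gap. A(no prior, history known) is not observed for the ward, so the terms cannot be separated at any sample size. The gap equals the missing-data term only if the case-mix term is zero, and nothing in the article supports that.

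**Illustrative size.** All inputs here are assumptions: 600 ward patients a day; 40% without prior admission; comorbidity count Poisson with mean 2 in the prior group and 0.3, 1 or 2 in the other; acute physiology normal with SD 1.0 in the prior group and 0.8 or 1.0 in the other; log-odds of the event = −7.2 + weight × comorbidity + 1.3 × physiology, with weight 0, 0.3 or 0.5; comorbidity entered as 0 for patients without prior admission; 4,000 simulated days. Selected results (case-mix term = gap − missing-data term; last digits reflect rounding):

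| Mean comorbidity, no prior | Weight | SD, no prior | AUC prior | AUC no prior, blank | Gap | Missing-data term | Case-mix term |
|---|---|---|---|---|---|---|---|
| 0.3 | 0 | 0.8 | 0.818 | 0.771 | 0.047 | 0.000 | 0.047 |
| 1 | 0 | 0.8 | 0.816 | 0.770 | 0.046 | 0.000 | 0.046 |
| 0.3 | 0.5 | 0.8 | 0.857 | 0.758 | 0.099 | 0.012 | 0.087 |
| 0.3 | 0.5 | 1.0 | 0.853 | 0.823 | 0.031 | 0.006 | 0.025 |
| 1 | 0.5 | 1.0 | 0.856 | 0.816 | 0.040 | 0.022 | 0.018 |
| 2 | 0.3 | 1.0 | 0.832 | 0.823 | 0.009 | 0.016 | −0.007 |
| 2 | 0.5 | 1.0 | 0.859 | 0.816 | 0.043 | 0.039 | 0.004 |

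Three settings with weight 0 and equal SD, where both terms are truly zero, gave gaps of 0.008, −0.010 and −0.007. Gaps therefore carry simulation noise of about 0.01. The last two rows, where the groups are alike in health, agree with a zero case-mix term within that noise. The first four rows do not.

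**Would the comorbidities from the notes do instead?** In the same simulation, extra ICU admissions caught in the daily top five per 28 days were compared between re-scoring only misclassified patients and re-scoring everyone (misclassification judged day by day, a simplification of the 48-hour rule):

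- mean 2, weight 0.5, SD 1.0: 7.392 against 2.744, ratio 2.7;
- mean 1, weight 0.5, SD 1.0: 1.414 against 0.448, ratio 3.2;
- mean 1, weight 0.3, SD 1.0: 0.854 against 0.154, ratio 5.5.

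The selected sample overstates the gain about 3- to 6-fold in these settings.

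**The case against.** The strongest defence is that reporting performance by prior-admission status answers a legitimate question: how well does the score work in patients whose history is unavailable? The risk score section asks exactly that. The article names no metric, no between-group difference and no rule for attributing one, and such detail may sit in a fuller document. This stands as a reason to keep the table. It does not rescue the stated purpose, because no choice of metric separates the two terms. Adjusting for recorded characteristics would not remove a difference in comorbidity, which is unrecorded in one group.

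The defence is also right that the article nowhere says the groups differ in health. Comorbidity treated at another hospital could also be hidden in the no-prior group. The difference is an inference from recent hospitalisation, and it is treated as such here.

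A reader might infer that the comparison will point the wrong way. In a separate illustrative run, a 40% wider spread of acute severity in the no-prior group gave AUCs of 0.825 (prior), 0.873 (no prior, blank) and 0.881 (no prior, known). The gap is 0.825 − 0.873 = −0.048, although history loss costs 0.881 − 0.873 = 0.008 (0.007 before rounding of the AUCs). Nothing in the article supports that wider spread, so the reversal is possible but not shown.

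A reader might also infer that re-scoring with the comorbidities extracted from the notes would measure the impact. The documents do not support this. Those data exist only for patients selected because HAVEN misclassified them, so re-scoring can show errors corrected but not correct classifications lost. The top-five list is relative, so unreviewed patients' ranks would move too. The notes review records the Clinical Frailty Score, which does not restore the score's Hospital Frailty Risk Score input.

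**Conclusion.** The concern holds in a limited form. The limitations section assigns the subgroup comparison a purpose that it cannot serve, because group membership and missingness coincide. Any difference found is an unknown mixture of missing inputs and case mix. This follows from the design and does not depend on the simulation.

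The size of the distortion is unknown. The AUC figures rest on assumed comorbidity levels, weights, spreads and event rates, and on absent history entering the score as zero; the article does not say how HAVEN encodes it. They show only that the gap can be well away from the true loss when the groups differ, and close to it when they do not.

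Severity is minor. The primary aim is to find candidate variables through the notes review, and no stated decision rests on this analysis. It would go too far to conclude that the sponsor will be misled, or that the groups certainly differ in health.

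**What to change.** In the strengths and limitations section, present the with/without table as a description of performance in each group, matching the risk score section.

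Assess the impact of missing data by a within-patient comparison. For all ward patients with prior admissions, set the comorbidity and frailty inputs to the values HAVEN uses when there is no prior admission, then re-score and re-rank the 09:00 list. Report the change in discrimination and in the number of unplanned ICU admissions captured by the top five. Each patient acts as their own control, so between-group case mix drops out.

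Re-scoring the reviewed FHR and FLR patients with comorbidities from the notes may be added, but only as a descriptive count of errors that missing comorbidity could explain. It would need the extracted comorbidities mapped to Elixhauser categories.

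The cost is one extra re-scoring run with no new patients, assuming the 09:00 inputs for the whole ward are kept or can be extracted again. The downside is that the result applies at the prior-admission group's comorbidity level and may not transfer directly to patients without prior admissions; the report should say so. If the run is not done, the minimum change is to drop the claim that the subgroup analyses assess the impact of missing data.

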### Implications

To the best of our knowledge, this is the first protocol to describe a study of this type. We hope this protocol will assist future development of similar systems.
